### Data collection and follow-up

All data will be recorded from an electronic case report form (eCRF) specifically elaborated for the study (eCRF CleanWEB, Telemedicine Technologies S.A.S., www.tentelemed.com, 2015) and will be recorded at four specific study’s times as follows: randomization (T0), baseline assessment (T1), delivery (T2), and at 6 months after delivery (T3). All assessments are based either on medical files (pregnancy and delivery characteristics, obstetrical and neonatal outcomes), face-to-face questionnaires (smoking and alcohol habits, personal hygiene, pregnancies history or symptoms, and concomitant treatments such as treatment with pessary or progesterone), phone calls (to collect data on vaginal symptoms or potential side-effects of antibiotic) or self-report (health outcomes of their infant and health service use during the 6 months following the initial hospitalization). Details of the data recorded at the different times of the study are given in Table 3.

**Table 3 Tab3:** Data collection, instruments and assessment times

At randomization (T0)	Data on the health status of the participant and pregnancy characteristics will be collected from medical files of the practitioners. A face-to-face questionnaire will be also completed by all women and filled out by the midwife/obstetrician to collect specific data on demographics characteristics, smoking and alcohol habits, previous pregnancies and personal hygiene. The first vaginal swab will be collected by the practitioner and send to one of the two point-of-care laboratories associated to the study.
At baseline assessment – (during screening and treatment phases - T1)	Subsequent vaginal swabs will be realized during either routine pregnancy consultation or at the woman’s home depending on each participant schedule. In this later case, the sample will be sent by the women to the referent POC laboratory using a stamped, self-addressed envelope. Symptoms and potential side effects of antibiotics will be collected via a telephone interview. Participants will be informed via a phone call for subsequent vaginal swabs and treatment intake if needed.

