### Sample size

The sample size was calculated from the expected differential ICER per preterm birth avoided between the two groups. In accordance with Briggs [22], the following hypothesis is stated: with an expected incremental rate of preterm birth of 1.3 % (4.3 % in the control group [23] and 3.0 % in the experimental group), an expected incremental cost of 230 euros (including cost of initial and following point-of-care tests and cost of treatments for 10 % of the women [24]), and an expected differential ICER at 22,500 euros corresponding to the avoided cost of a preterm birth before 37 weeks [25], with an 80 % statistical power and a threshold for statistical significance set at a *P* value of 0.05, and assuming that a potential 20 % of patients will be lost to follow-up, these calculations showed that 6,800 patients are needed (3,400 per group). Considering the potential of inclusion of each participating center, the inclusion duration will be planned over a 12-month period. The maximal period of participation for the included women is 12 months.

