### Statistical analysis

The data will be analyzed using SPSS version 20.0 software. Statistical significance is defined as *P* < 0.05. The methodology will be based on the Consolidated Standards of Reporting Trials Statement (CONSORT, http://www.consort-statement.org/consort-statement/) [26]. The full analysis population (including all subjects who will be randomized and will be at least evaluated at baseline) will be used in the primary analysis and the per protocol population (including all subjects who will be randomized and will not have major protocol deviations) will be used in the secondary analysis to assess the reliability of the results. Finally, missing data will be handled where possible using multiple imputations, and a sensitivity analysis will be performed. No interim analysis is planned.

The normality of the parameters will be estimated using frequency histograms and the Shapiro test. In case of nonparametric distribution, the data will be log transformed to obtain a normal distribution or nonparametric bootstrapping performed for cost data. In accordance with the distribution of the parameters, the baseline parameters will be presented separately for the control group and the experimental group: mean (standard deviation) or median (interquartile range) for continuous variables, proportions for categorical variables. Then, data will be compared between the two groups using Student’s t-test for continuous variables (durations), and chi-square or Fisher’s exact tests for categorical variables.

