### Cost-effectiveness analysis

Incremental cost-effectiveness ratios (ICER) will be used to compare the cost and effectiveness of the experimental strategy with usual care. The ICER is the ratio of the difference between groups in costs to the difference in effectiveness. The difference in effectiveness equals the number of preterm births averted and is calculated as the number of preterm births in the screening group minus the number of preterm births in the control group. Thus, the ICER provides information on the potential acceptability of the intervention for decision makers. The costs perspective taken in our economic analysis is that of the healthcare payer. The time horizon started from the first prenatal consultation before the 20 weeks of gestation and ended at 6-months of age or death. The healthcare costs included are those that are likely to differ across the intervention and control groups. In our study, these costs are those associated with: screening using the point-of-care procedure (quantitative molecular analysis), control vaginal swabs for positive women, antibiotic treatments, antenatal hospital admissions, physicians’ consultations, management of complications, as well as neonatal costs for full term infants and preterm infants. Unit costs for health service use will be estimated using data from the French National Hospital Database (Programme de médicalisation des systèmes d’information, PMSI) and the National Tariff. Treatment costs were obtained from the French register of pharmaceutical specialties, an online database of information on healthcare products. The cost of the POC analysis using quantitative real-time PCR (qPCR) will be calculated using micro-costing technique, which is particularly well suited to evaluating the cost of an emerging technique [27]. The volume of resources used will be determined by direct observation of each stage of each testing procedure. Fixed and variable costs will be included. All resources will be valued in 2015/2016 euros, and the 12-month trial means there is no requirement to apply discounting. As the cost of preterm birth differs significantly according to the gestational age at birth [28–30], we will attempt to address this issue by calculating an ICER for specific birth gestational ages. Probabilistic sensitivity analyses, using the non-parametric bootstrap method, will be carried out to generate mean expected ICERs and to determine whether uncertainty or variation in the data used affect the ICERs [31]. In addition, cost-effectiveness acceptability curves were constructed to represent decision uncertainty surrounding cost-effectiveness estimates [32].

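### The stated comparisons are unadjusted although prognostic data are recorded at randomization; pre-stating covariate adjustment would bring a small gain at little cost

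*Protocol article*

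**What the plan says.** The Statistical analysis section of the protocol article names the between-group tests: Student's "t-test for continuous variables (durations), and chi-square or Fisher" exact tests for categorical variables. The sentence follows one on the presentation of baseline data, but its reference to durations fits the secondary outcomes (length of hospitalization, intensive care stay and ventilation).

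The primary endpoint is the ICER. The Cost-effectiveness analysis section defines it: "The ICER is the ratio of the difference between groups in costs to the difference in effectiveness". It then takes the effectiveness difference as the count of preterm births in one group minus the count in the other. Uncertainty is handled by non-parametric bootstrap and acceptability curves. No covariate is mentioned in either section.

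Table 3 lists a face-to-face questionnaire at T0 "to collect specific data on demographics characteristics, smoking and alcohol habits, previous pregnancies and personal hygiene". It also says that pregnancy characteristics are taken from the medical files. Gestational age at entry is not itemized, but it must be known to check eligibility (under 20 weeks) and is presumably among them.

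**The concern.** Some of the variables recorded at T0 can be expected to predict preterm birth and may also predict cost. If they enter no analysis, the estimates carry variance that could have been removed, and a chance imbalance in a predictor passes unchanged into the risk difference. That difference is the denominator of the primary endpoint and is planned at only 1.3 points, so small movements in it are magnified in the ratio. The covariates also have to be named in advance: the trial is open-label, and covariates chosen after the results are known would look selective. The question is how much is lost in practice.

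**Working it through.** **Inputs from the Sample size section.** Rates are 4.3% in the control group "and 3.0 % in the experimental group", a difference of 1.3 points. The calculation is "with an 80 % statistical power" and a "threshold for statistical significance set at a *P* value of 0.05", with sidedness not stated. It also uses "an expected incremental cost of 230 euros", 20% loss and 3,400 women per group, hence 3,400 × 0.8 = 2,720 evaluable per group.

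**Inputs assumed, because the documents give none.** Three binary covariates with prevalences of 20%, 50% and 25%, and odds ratios for preterm birth between 1.3 and 2.0.

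**1. The plan's own figure.** The article describes an ICER-based calculation with "an expected differential ICER at 22,500 euros". It cannot be rebuilt, because no cost SD or cost-effect correlation is given. As a plain comparison of 4.3% with 3.0% at 80% power, a one-sided 0.05 test with continuity correction needs 2,724 per group. Then 2,724 / 0.8 = 3,405 per group, or 6,810 in total, against the stated 6,800. The two-sided version without correction gives 8,166. The match is numerical only. Power below is two-sided.

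**2. Power without adjustment.**
- SE of the difference = √[(0.043 × 0.957 + 0.030 × 0.970) / 2,720] = 0.00508, or 0.51 points.
- SE under the null (mean rate 3.65%) = √[2 × 0.0365 × 0.9635 / 2,720] = 0.00509.
- Power = Φ[(0.013 − 1.96 × 0.00509) / 0.00508] = Φ(0.60) = 72.5%.

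**3. Power with adjustment.** R² = var(p) / [0.043 × 0.957], where p is the risk across the eight covariate patterns, with the intercept set so that the mean risk is 4.3%. Adjustment is approximated as variance × (1 − R²), that is, as 2,720 / (1 − R²) women per group. The equivalent number of extra women is 6,800 × R² / (1 − R²).

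| Odds ratios | R² | Equivalent women | Power |
|---|---|---|---|
| 1.5, 1.3, 1.3 | 0.27% | 18 | 72.6% |
| 1.8, 1.5, 1.5 | 0.64% | 44 | 72.7% |
| 2.0, 2.0, 2.0 | 1.48% | 102 | 73.1% |

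The gain is 0.1 to 0.6 points. Even an R² of 5%, well above these scenarios, would give only 74.6%.

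**4. Chance imbalance.** For a covariate with 20% prevalence, the SD of the between-group difference in prevalence is √(2 × 0.2 × 0.8 / 2,720) = 1.08 points, so two SDs are 2.17 points. The shift in the risk difference is the imbalance times the covariate's own risk difference (mean risk held at 4.3%):
- Odds ratio 1.5 (5.8% v 3.9%, 1.85 points): 0.0217 × 1.85 = 0.040 points, 3% of 1.3.
- Odds ratio 2.0 (7.0% v 3.6%, 3.4 points): 0.0217 × 3.4 = 0.073 points, 6% of 1.3.

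**5. Carried into the ICER (illustration, cost difference held at 230 euros).** The planning inputs give 230 / 0.013 = 17,700 euros. The larger shift moves this to 230 / 0.01373 = 16,800 or 230 / 0.01227 = 18,700 euros. One ordinary standard error of the risk difference moves it much further, to 230 / 0.01808 = 12,700 or 230 / 0.00792 = 29,000 euros.

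**6. Costs.** With no cost SD and no covariate-cost association in the documents, the gain for the cost difference cannot be calculated.

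**The case against.** The strongest objection is that nothing here is wrong. Unadjusted comparison is valid under 1:1 randomization, and chance imbalance is already part of the sampling error: the worst shift above, 0.073 points, is about 0.14 of the 0.51-point standard error. A covariate list is also something that a condensed article commonly leaves to the full protocol or analysis plan, neither of which is shown. All of this stands, and it confines the point to a suggestion. What remains is that the article states a method, named tests and a difference in counts, and that this method is crude.

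Three stronger readings are tempting but not supported:
- **That crude two-sample tests are the whole analysis.** The primary endpoint is a bootstrapped ICER, and the named tests bear mainly on secondary outcomes. The bootstrap expresses uncertainty and does not itself adjust, but the text does not exclude adjustment.
- **That gestational age at entry fixes the period over which antenatal costs accrue.** The cost horizon starts at the first prenatal consultation and not at randomization. Recruitment is planned at a first-trimester visit, which narrows the expected spread. The variable itself is only inferred to be among the T0 data.
- **That a strong predictor is being ignored.** Women with previous preterm birth, late miscarriage, diabetes, treated hypertension, conization or multiple pregnancy are not eligible, so these strong risk factors cannot be imbalanced.

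**Conclusion.** The point holds as a minor improvement. The comparisons stated in the article are unadjusted, prognostic data are already recorded at T0, and adjustment would help slightly. For preterm birth the gain is 0.1 to 0.6 points of power from a base of 72.5% (two-sided, 2,720 per group), plus removal of a shift of about 3 to 6% of the planned effect in a two-SD imbalance. Both figures rest on assumed prevalences and odds ratios and on the variance × (1 − R²) approximation. A gain for costs is plausible but cannot be sized. A reader might infer that the crude analysis is biased or that the trial's conclusion is at risk; neither follows. Use of centre, the stratification factor, in the analysis is a separate matter.

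**What to change.** Pre-state a short list of T0 covariates, for example smoking, previous pregnancies, maternal age and, if recorded, gestational age at randomization. Estimate the preterm-birth difference by logistic regression on group and these covariates, reported as a standardized risk difference. Estimate the cost difference by regression on the same covariates. Bootstrap the two models jointly, so that the ICER and the acceptability curve use adjusted differences and keep the correlation between cost and effect. Retain the crude comparison as a sensitivity analysis. If the full analysis plan already adjusts, it is enough to align the wording.

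The cost is wording and somewhat more analysis work: specifying a model for cost data that may be non-normal, and handling missing covariates within the planned multiple imputation. No new data collection is needed, provided that gestational age at entry is in fact recorded.

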### Cost-effectiveness analysis

Incremental cost-effectiveness ratios (ICER) will be used to compare the cost and effectiveness of the experimental strategy with usual care. The ICER is the ratio of the difference between groups in costs to the difference in effectiveness. The difference in effectiveness equals the number of preterm births averted and is calculated as the number of preterm births in the screening group minus the number of preterm births in the control group. Thus, the ICER provides information on the potential acceptability of the intervention for decision makers. The costs perspective taken in our economic analysis is that of the healthcare payer. The time horizon started from the first prenatal consultation before the 20 weeks of gestation and ended at 6-months of age or death. The healthcare costs included are those that are likely to differ across the intervention and control groups. In our study, these costs are those associated with: screening using the point-of-care procedure (quantitative molecular analysis), control vaginal swabs for positive women, antibiotic treatments, antenatal hospital admissions, physicians’ consultations, management of complications, as well as neonatal costs for full term infants and preterm infants. Unit costs for health service use will be estimated using data from the French National Hospital Database (Programme de médicalisation des systèmes d’information, PMSI) and the National Tariff. Treatment costs were obtained from the French register of pharmaceutical specialties, an online database of information on healthcare products. The cost of the POC analysis using quantitative real-time PCR (qPCR) will be calculated using micro-costing technique, which is particularly well suited to evaluating the cost of an emerging technique [27]. The volume of resources used will be determined by direct observation of each stage of each testing procedure. Fixed and variable costs will be included. All resources will be valued in 2015/2016 euros, and the 12-month trial means there is no requirement to apply discounting. As the cost of preterm birth differs significantly according to the gestational age at birth [28–30], we will attempt to address this issue by calculating an ICER for specific birth gestational ages. Probabilistic sensitivity analyses, using the non-parametric bootstrap method, will be carried out to generate mean expected ICERs and to determine whether uncertainty or variation in the data used affect the ICERs [31]. In addition, cost-effectiveness acceptability curves were constructed to represent decision uncertainty surrounding cost-effectiveness estimates [32].

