### Endpoints

#### Primary endpoint

The primary endpoint is the incremental cost-effectiveness ratio (ICER), expressed as the extra cost per additional preterm birth avoided before 37 weeks. The effectiveness criterion has been discussed and consensually approved by all the study’s main partners (gynecologist coordinator and co-coordinators, biologists, health economist and methodologist). We can assume that this intermediary criterion properly reflects short- and long-term prognosis of the children [20, 21].

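### The ICER denominator is written as screening minus control, the opposite sign to births averted, and in counts that are safe only with total costs and equal arms

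*Protocol article*

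**What the plan says.** All references are to the protocol article.

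- **Primary endpoint section:** the ICER is "expressed as the extra cost per additional preterm birth avoided before 37 weeks".
- **Cost-effectiveness analysis section:** "The ICER is the ratio of the difference between groups in costs to the difference in effectiveness". It continues: "The difference in effectiveness equals the number of preterm births averted", and the same sentence then says that this difference "is calculated as the number of preterm births in the screening group minus the number of preterm births in the control group". The section does not say whether the cost difference is an arm total or a mean per woman.
- **Sample size section:** the planning rates are "4.3 % in the control group [23] and 3.0 % in the experimental group", a difference of 1.3 points. Planned alongside them are "an expected incremental cost of 230 euros" and "an expected differential ICER at 22,500 euros corresponding to the avoided cost of a preterm birth before 37 weeks".
- **Cost-effectiveness analysis section, on the bootstrap:** probabilistic sensitivity analyses by non-parametric bootstrap "will be carried out to generate mean expected ICERs". Acceptability curves are also planned.

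**The concern.** A preterm birth is averted when it would occur under usual care but not under screening, so the number averted is control minus screening. The protocol names that quantity and then gives the formula for its negative. Label and formula cannot both be followed.

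The ratio is the primary endpoint, and its sign carries the message. Followed literally, a programme that costs more and works gets a negative ICER, which can be read as cost-saving and effective. A programme that costs less and works, which is what the Abstract hypothesises, gets a positive ICER, which reads as a price to be paid per birth avoided. Comparison with the 22,500 euro reference also fails, because every costlier, effective programme falls below it however expensive it is. If the same effect variable feeds the bootstrap and the acceptability curves, they inherit the error.

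A smaller matter sits in the same sentence. The difference is in numbers of births, whereas the Sample size and Secondary endpoints sections use rates. A count in the denominator is coherent only with a matching total cost in the numerator and arms of equal size.

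**Working it through.** **Inputs.** From the Sample size section: preterm birth 4.3 % (control) and 3.0 % (experimental), incremental cost 230 euros, 3,400 women per group, 20 % loss. The 230 euros is read here as a cost per woman; the article does not say so explicitly.

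**Step 1: the plan's own direction.** The stated difference of 1.3 points is 4.3 - 3.0, that is, control minus experimental. The sample-size reasoning therefore subtracts the opposite way to the formula in the Cost-effectiveness analysis section.

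**Step 2: the formula as written.** Expected preterm births are 3,400 × 0.030 = 102.0 (screening) and 3,400 × 0.043 = 146.2 (control).

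- As written: 102.0 - 146.2 = -44.2 births averted.
- Control minus screening: 146.2 - 102.0 = +44.2.
- With 80 % evaluable (2,720 per group) the values are 81.6 - 117.0 = -35.4 and +35.4.

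**Step 3: the ICER at planning values.**

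- As written: 230 / (0.030 - 0.043) = -17,692 euros.
- Corrected: 230 / (0.043 - 0.030) = +17,692 euros per preterm birth avoided.

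**Step 4: the other sign combinations.** The same magnitudes are used with signs changed, purely as illustration. Cost difference is screening minus control.

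| Screening is | Cost difference | Preterm, screening / control | ICER as written | ICER corrected |
|---|---|---|---|---|
| costlier, effective | +230 | 3.0 % / 4.3 % | -17,692 | +17,692 |
| cheaper, effective | -230 | 3.0 % / 4.3 % | +17,692 | -17,692 |
| costlier, harmful | +230 | 4.3 % / 3.0 % | +17,692 | -17,692 |

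At an illustrative 1,000 euros extra per woman, the corrected ICER is 1,000 / 0.013 = 76,923, well above 22,500. The written rule gives -76,923, below it.

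**Step 5: counts against rates, with the sign corrected.**

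- Total costs, equal arms: 230 × 3,400 / 44.2 = 17,692. This equals the rate-based ICER, so counts do no harm here.
- Mean cost per woman over a count: 230 / 44.2 = 5.2 euros, which is meaningless.
- Total costs, unequal analysed arms, assumed 2,650 screening and 2,790 control: births averted = 119.97 - 79.5 = 40.47. With an assumed control cost of 1,000 euros per woman, (1,230 × 2,650 - 1,000 × 2,790) / 40.47 = about 11,600 euros. With 3,000 euros per woman, (3,230 × 2,650 - 3,000 × 2,790) / 40.47 = about 4,700 euros. Rates with mean costs still give 17,692.

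The arm sizes and control costs in the last line are assumptions. They show that the result depends on a choice the text leaves open; they do not forecast its size.

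**The case against.** **The intention is not in doubt.** The sentence itself names births averted, the endpoint section speaks of births avoided, and the planning rates show the direction. Swapping two terms repairs it; the absolute value, design, data and sample size are untouched. All of this stands, and an alert analyst would probably correct the slip. It limits the point to a correction of wording, but the written rule for a primary endpoint should not depend on silent correction.

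**The cost difference is given no direction in the formula.** If costs were also subtracted in the opposite sense (control minus screening), the ratio would come out at -230 / -0.013 = +17,692. The endpoint definition closes this route: extra cost means screening minus control.

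**Counts are harmless under 1:1 allocation with total costs.** True, as step 5 shows. A reader might go further and infer that unequal loss to follow-up will create or hide averted births. The article does not support that as a stated defect. It gives only an overall 20 % loss, with no split by arm, and the Statistical analysis section plans multiple imputation where possible. The count point is therefore conditional.

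**The bootstrap.** A reader might infer from "will be carried out to generate mean expected ICERs" that the primary ICER will be the average of replicate ratios. The article does not say so. It defines the ICER as a ratio of differences, places the bootstrap under probabilistic sensitivity analyses, and in the Abstract assigns it to uncertainty. The phrase is ambiguous and can equally mean a ratio of mean differences. A clarification is still worthwhile, because averaging ratios would matter if done. In a simulation at the planned effect with 2,720 per arm (cost SD assumed between 1,000 and 5,000 euros, cost and effect independent), the mean of ratios was about 22,000 euros against 17,692. That describes a possible misreading, not the plan.

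**Conclusion.** The sign error holds. The denominator formula contradicts its own label, the primary endpoint definition and the direction of the planning rates. At planning values it turns +17,692 into -17,692 euros per preterm birth avoided, and it gives a positive ratio to a cheaper, effective programme. This rests on the article's own rates and on reading 230 euros as a cost per woman; the reversal of sign does not depend on that reading.

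The use of counts holds conditionally: it is equivalent to rates if costs are arm totals and the analysed arms are equal in size, and wrong otherwise. The article fixes neither condition. Nothing in it makes a mean of bootstrap ratios the primary result, and nothing in it supports a specific error from differential loss. Because the slip is in the stated rule for the primary endpoint, it should be corrected before the analysis, even though the remedy is small.

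**What to change.** In the Cost-effectiveness analysis section, replace the formula with three definitions:

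- effect difference = proportion with preterm birth before 37 weeks in control minus the proportion in screening;
- cost difference = mean cost per woman in screening minus mean cost per woman in control;
- ICER = cost difference divided by effect difference, as a ratio of these two mean differences.

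Use the same orientation for the ICERs at other gestational ages. As a clarification, add that the bootstrap serves uncertainty (the joint cost-effect scatter and the acceptability curves) and that the point estimate is not an average of replicate ratios.

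The cost is one paragraph of wording, with no extra data and no change to design or sample size.

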**Methods/Design:**

A multicenter, open-label randomized controlled trial (RCT) will be conducted in which 20 French obstetrics and gynecology centers will recruit eligible pregnant women at less than 20 weeks gestation with singleton pregnancy and with a low-risk factor for preterm birth. Interventions will include a) an experimental group that will receive a systematic rapid screen-and-treat program from a point-of-care analysis using a molecular quantification method and b) a control group that will receive usual care management. Randomization will be in a 1:1 allocation ratio. The primary endpoint that will be assessed over a period of 12 months will be the incremental cost-effectiveness ratio (ICER) expressed as cost per avoided preterm birth before 37 weeks. Secondary endpoints will include ICER per avoided preterm birth before 24, 28 and 32 weeks, obstetrical outcomes, neonatal outcomes, rates of treatment failure and recurrence episodes for positive women. Uncertainty surrounding these estimates will be addressed using nonparametric bootstrapping and represented using cost-effectiveness acceptability curves. A total of 6,800 pregnant women will be included.

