#### Secondary endpoints

The secondary endpoints are as follows:ICER per preterm birth avoided before 26, 28, 32 and 34 weeks.Obstetrical outcomes: rates of preterm birth before 26, 28, 32, 34, and 37 weeks of gestation, spontaneous abortion (between 14-22 weeks), late miscarriage (between 22-24 weeks), premature rupture of membranes, severe intrauterine growth restriction, preterm labor, duration of the woman’s hospitalization (that is hospitalization for delivery or preterm labor and potential previous hospitalizations due to gynecologic complications during pregnancy).Neonatal outcomes: neonatal mortality, neonatal morbidity (respiratory distress syndrome, bronchopulmonary dysplasia, necrotizing enterocolitis, periventricular leukomalacia), transfer to a neonatal intensive care unit (duration), mechanical ventilation (duration), congenital anomalies and duration of the newborn’s hospitalization.Treatment effectiveness: rate of recurrence (defined as a positive control vaginal swab using qPCR after the negativation of a precedent control vaginal swab), rate of treatment failure (defined as *A. vaginae* > 10^8^ copies/mL and/or a *G. vaginalis* load ≥ 10^9^ copies/mL from a control vaginal swab) and side effects associated with treatment.Other health care utilization: all the mother’s use of health care during the whole study period (for example, gynecologists and general practitioner consultations, hospital admission, clinical examinations and medications), as well as health care for the newborn (including neonatal care, re-hospitalization, medications, planned and non-planned consultations with pediatric practitioner or other specialists).

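### The secondary ICERs by gestational cut-off rescale one total cost difference, so they cannot show how cost varies with gestational age; before 26 and 28 weeks a bootstrap mean ratio is not interpretable

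*Protocol article*

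**What the plan says.** The Cost-effectiveness analysis section gives one definition: "The ICER is the ratio of the difference between groups in costs to the difference in effectiveness". Its list of included costs runs from screening, control swabs and antibiotics through antenatal care to "management of complications, as well as neonatal costs for full term infants and preterm infants". It then motivates the further ratios ("As the cost of preterm birth differs significantly according to the gestational age at birth") and gives the remedy: "we will attempt to address this issue by calculating an ICER for specific birth gestational ages".

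The Secondary endpoints section lists these ratios as "ICER per preterm birth avoided before 26, 28, 32 and 34 weeks". The abstract has a different set: "ICER per avoided preterm birth before 24, 28 and 32 weeks". Neither place restricts or re-costs the numerator by cut-off. Uncertainty is to be handled by sensitivity analyses "using the non-parametric bootstrap method, will be carried out to generate mean expected ICERs", together with acceptability curves.

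The Sample size section supplies the planning figures: preterm birth in "4.3 % in the control group [23] and 3.0 % in the experimental group", an incremental cost of 230 euros for tests and treatments, 22,500 euros as the avoided cost of a preterm birth before 37 weeks, and 3,400 women per group with 20% lost to follow-up. No expected rate is given for any cut-off other than 37 weeks.

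**The concern.** The stated aim is to deal with costs that vary by gestational age. The stated calculation changes only the effect unit. The numerator stays the same total at every cut-off, so it includes savings from later births that the denominator leaves out. A reader could take the 28-week ratio as the price of avoiding a birth before 28 weeks and set it against the cost of such a birth, which the ratio does not support.

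There is also a numerical problem. Before 26 and 28 weeks, events in a low-risk population are likely to be so few that the denominator can easily be zero or have the wrong sign. An average of bootstrap ratios then has no usable meaning.

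**Working it through.** **Inputs.** From the Sample size section: 4.3% v 3.0% (difference 0.013), 230 euros, 22,500 euros, and 3,400 x 0.8 = 2,720 evaluable women per arm. Assumed, because the documents give no distribution: the share s(k) of births before 37 weeks that fall before week k, and the same relative reduction at every gestation. Births averted are counted as control minus experimental.

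**The plan's own figures.** The plan prints no value for any cut-off ICER, so there is none to reproduce. Its inputs imply, for 37 weeks and test-and-treatment cost only, 230 / 0.013 = 17,692 euros per birth averted. The sample size is not at issue here.

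**Step 1: what the ratio measures.** With one numerator dC and a constant relative effect, the risk difference before week k is s(k) x 0.013. Hence

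ICER(<k) = dC / (s(k) x 0.013) = ICER(<37) / s(k).

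This identity holds whatever dC is. The cost of births before week k does not appear in it except inside the common total dC.

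**Step 2: what the numerator leaves unmatched.** Births averted before 37 weeks per 2,720 women: 2,720 x 0.013 = 35.4. With s(28) = 3-8%, 1.1-2.8 of these fall before 28 weeks. The other 32.5-34.3 affect the numerator but are not counted in the denominator.

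**Step 3: direction depends on the sign of dC.** Two values can be formed from the plan:

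- tests and treatment only: dC = +230 euros per woman;
- net of avoided preterm-birth cost: dC = 230 - 22,500 x 0.013 = 230 - 292.5 = -62.5 euros per woman.

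| Cut-off | Assumed share | ICER if dC = +230 | ICER if dC = -62.5 |
|---|---|---|---|
| <37 | 100% | 17,692 | -4,808 |
| <34 | 20-35% | 88,462 to 50,549 | -24,038 to -13,736 |
| <32 | 10-20% | 176,923 to 88,462 | -48,077 to -24,038 |
| <28 | 3-8% | 589,744 to 221,154 | -160,256 to -60,096 |
| <26 | 1.5-5% | 1,179,487 to 353,846 | -320,513 to -96,154 |

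The relative effect is identical in every row. Only the share and the sign of dC move the ratio.

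**Step 4: stability of the denominator.** The number averted has expectation 2,720 x 0.013 x s and standard error sqrt(2,720 x [a(1-a) + b(1-b)]), with a = 0.043s and b = 0.030s. For example, s = 5% gives 5.8 v 4.1 births, 1.77 averted, standard error 3.15. The probability that the observed difference is zero or reversed comes from 400,000 simulated pairs of binomial counts, with the planned effect true.

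| Cut-off | Births averted | Standard error | P(zero or reversed) | P(exactly zero) |
|---|---|---|---|---|
| <37 | 35.4 | 13.8 | 0.6% | 0.1% |
| <34 | 7.1-12.4 | 6.3-8.3 | 15-7% | 3-2% |
| <32 | 3.5-7.1 | 4.5-6.3 | 25-15% | 7-3% |
| <28 | 1.1-2.8 | 2.4-4.0 | 41-28% | 15-8% |
| <26 | 0.5-1.8 | 1.7-3.2 | 50-34% | 24-11% |

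Before 26 and 28 weeks the expected number averted is below its standard error throughout the assumed range. Bootstrap resamples of such data will often have a zero denominator, where the ratio does not exist, or one of the opposite sign. Their mean is then governed by those resamples.

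**The case against.** **The numerator of the secondary ratios is inferred.** The article does not spell it out, the remedy is worded as an attempt, and the phrase about specific gestational ages could mean bands. That is fair as to wording. But the article gives one definition and one cost list, and bands do not rescue it: each band would still carry the full cost difference, over a denominator no larger in expectation than that of the cumulative cut-off at its upper limit.

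**Total cost over another effect unit is a legitimate ICER.** This stands. A decision maker may pay more per birth avoided before 32 weeks than per birth avoided before 37. Neonatal cost variation also enters the numerator already. The fault is the claim that these ratios handle gestational-age-specific cost.

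**Other outputs cover the gap.** The preterm birth rates at each cut-off are separate secondary outcomes, so the sparse counts will be visible. Acceptability curves built on net benefit would avoid division by zero. They would still set the whole cost difference against a subset of births, and the article does not say at which cut-offs they will be drawn.

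**Stronger readings that do not hold.** A reader might infer that the ratios will make the programme look less efficient at early gestations. That follows only if the total cost difference is positive. The 230 euros excludes the neonatal costs that the numerator must contain, and on the plan's own 22,500 euros the sign reverses. A reader might also infer that all four ratios are near-undefined and should be dropped. On the assumed shares, the 32- and 34-week ratios are imprecise (zero or reversed in 7-25% of trials) but usable with intervals. Deleting listed endpoints after recruitment has begun would be a debatable step.

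**Conclusion.** The concern holds in a limited form. Followed as written, the cut-off ICERs rescale a single cost difference and cannot meet the aim the article gives for them. That conclusion needs only the stated definition and cost list; the exact scaling by 1/share also assumes a constant relative effect. Before 26 and 28 weeks the denominator is zero or reversed in about 28-50% of trials even if the planned effect is true, so a mean bootstrap ICER is not interpretable there. That second conclusion rests on assumed shares of 1.5-8%, 2,720 evaluable women per arm and a constant relative effect.

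The euro values in the table illustrate scaling and sign only; they are not forecasts. These are secondary endpoints, and neither the primary ICER before 37 weeks nor the sample size is affected.

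**What to change.** 1. Address gestational-age-specific cost directly, with a table by arm in mutually exclusive bands (for example <26, 26-27, 28-31, 32-33, 34-36 and >=37 weeks). Show the number of births, the risk difference with 95% CI, the mean cost per birth, and the band's contribution to the total cost difference per randomised woman. Add a row for pregnancy losses not counted as births, so that the contributions sum to the primary ICER numerator. Mean costs within a band are descriptive, because gestational age at birth is a post-randomisation outcome.
2. Keep the listed cut-off ICERs as descriptive, and state that each carries the full cost difference.
3. Before 26 and 28 weeks, report the cost difference and the risk difference with intervals, or net benefit, in place of a mean bootstrap ratio.
4. Reconcile the cut-offs in the abstract (24, 28, 32) with those in Secondary endpoints (26, 28, 32, 34).

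The cost is small. Gestational age and resource use are already to be collected, and no endpoint is removed. It takes a little more analysis and gives the early-cut-off ratios less prominence. The wording should be settled before outcomes are compared by arm.
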